### Sampling procedure and selection of participants

Sampling of health Units: The study will use purposive sampling to include Aber Hospital, Aboke HCIV and Atipe HCIII as the site for enrollment. This is based on the following criteria:Already existent good laboratory capacity for diagnosis of malaria.Presence of an experienced microscopist.Antenatal care visit volumes of at least 50 visits per month.Good quality of routine service offered to patients with malaria as per periodic quality of care assessment.

Participants coming to the sampled in healthcare facilities that will meet the eligibility criteria will be included in the study. Consecutive enrollment of participants will be undertaken up to when the minimum sample size required for the study will be met.

### Study procedures

#### Microscopy

Thick and thin blood smears will be stained with 2% Giemsa and read by experienced laboratory technologists. Parasite densities will be calculated by counting the number of asexual parasites per 200 leukocytes (or per 500 leukocytes, if the count is < 10 asexual parasites/200 leukocytes), assuming a leukocyte count of 8000/µl. A blood smear will be considered negative when the examination of 100 high power fields does not reveal asexual parasites. Gametocytemia will also be determined from thick smears. Thin smears will be used for parasite species identification. At the time of delivery, recruited women will be screened for parasitemia on placental blood. This will be done by microscopy, with the same methods described above.

#### Molecular diagnosis and Plasmodium species confirmation

The blood samples of the patients will be collected using filter paper (Whatman 3 MM) during admission to the healthcare facility. The dried blood spots (DBSs) will be collected through a finger prick (three drops of blood per participant) on filter papers which will be dried and kept in plastic bags with desiccant and stored in boxes in a cool dry place at room temperature before being transferred at the ISS for molecular diagnosis and drug resistance analysis.

#### Shipment of the blood samples

The collected blood samples will be shipped to Italy for advanced polymorphism analysis. During shipment, all the samples will be stored in a dry, cool place at room temperature to the Italian National Institute of Health (Istituto Superiore di Sanità, ISS). To enhance local capacity building, one laboratory person from Aber hospital will attend a two weeks exposure at the reference laboratory in Italy.

#### Advanced analysis of polymorphism

Total genomic DNA will be extracted from filter blots (3MM Whatman) using the PureLink Genomic DNA Kits-Invitrogen, according to the manufacturer’s recommendation. Parasite identification is based on nested PCR assay targeting the 18S rRNA gene [23]. The 18S rRNA gene is used as a target since it contains both highly conserved and variable regions for each *Plasmodium* species. The genus-specific PCR will be followed by *Plasmodium* species-specific PCR amplification. Amplicons from the second PCR will be separated by electrophoresis on a 2% agarose gel and stained with ethidium bromide for visualization using ultraviolet trans-illumination. The presence of parasitaemia will be confirmed when the expected band size corresponding to *P. falciparum*, *P. vivax, P. malariae and or P. ovale* will be identified.

#### Assessment of Plasmodium falciparum drug resistance.

Target *P. falciparum* drug resistance genes: *Pfk13* propeller, *Pfdhfr* and *Pfdhps*.

The polymorphisms analysis of the propeller domain of the *Pfk13* gene will be performed by PCR amplifications and subsequent sequencing. Analysis of *Pfdhfr* gene at codons 51, 59, 108 and *Pfdhps* gene at codon positions 436, 437, 540, 581, 613 will be done by means of amplifications and subsequent Sanger sequencing. Commercial oligonucleotide primer pairs for *Pfk13* will be obtained based on the published article by Taylor et al. [24], whereas for the analysis of *dhfr* and *dhps* genes primer pairs will be obtained based on the published article by Menegon et al. [25]. The obtained sequences will be compiled and analyzed by Accelrys DS Gene software. PlasmoDB gene identification no. PF3D7_1343700 (*P. falciparum* 3D7 strain) will be used as reference in the numbering of nucleotide and amino acid positions. Molecular studies will be performed only for research purposes and will have no impact on the clinical management of study patients.

#### HIV and syphilis screening

HIV and Syphilis will be measured according to the Uganda National Guidelines [19]

#### Blood glucose

Blood glucose will be measured by Glucometer “Accu-Chek Active”, Narang Medical LTD.

#### Hemoglobin levels

Blood haemoglobin levels will be measured by Hemoglobin Testing System “Mission Ultra Hb”, Narang Medical LTD.

### Data analysis

For descriptive purposes continuous and ordinal variables data will be expressed as median with interquartile range. For categorical variables, percentages are calculated. Student’s t-test or analysis of variance (ANOVA) will be used to compare normally distributed numerical variables. Mann Whitney U-tests and Kruskal–Wallis tests will be used to compare numerical variables when normality cannot be assumed, while chi-squared tests will be used to compare categorical variables.

Association analysis will be carried out to identify risk factors for Plasmodium infection and adverse maternal or foetal outcomes. We will compare behavioural factors and adherence to IPTp (and type of IPTp regimen) to the incidence of symptomatic/severe malaria and adverse neonatal or foetal outcomes (miscarriage, stillbirth, low birthweight). Multivariable logistic regression models will be used to identify independent risk factors for the same clinical outcomes. A forward and backwards stepwise approach will used to include variables into the models, with a limit of P < 0.2.

A P-value of < 0.05 will be considered statistically significant. Final analyses will be conducted after the end of patient recruitment while interim analyses are planned at half 7 months from the incipit. Statistical analysis will be performed with R-software (R Foundation for Statistical Computing, Vienna, Austria).

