### Sample size estimation

#### Sample size estimation

COVID-19 impact population

For the retrospective cohort investigating the impact of COVID-19, we shall use a *facility-based census* to include all pregnant mothers who sought care at the study sites for the period January 2018 to December 2021.Prospective çohort of pregnant women

For the prospective cohort, the sample size was estimated using the sample size estimation function in STATA12 for two-sample comparison of proportions. Null hypothesis: p1 = p2, (no difference in preterm birth rates), where p1 is the preterm birth rate among pregnant mothers diagnosed with malaria (exposed group) and p2 is the preterm birth rate among pregnant mothers with no diagnosis of malaria (non-exposed group). Assuming a type I error, alpha, of 0.050 for two-sided hypothesis, power of the study at 0.80, p1 = 0.075 and p2 = 0.039 based on the preterm birth rates reported in the Uganda Birth Cohort Study conducted from 2014–2016 in 12 districts in rural northern and southwestern Uganda [20]. Assuming equal number of participants in both groups, the required sample sizes in each of the two groups is 705. And after factoring in 10% for non-response in both groups, the total minimum required sample size is 1552 pregnant women (776 in each of the 2 groups).Antimalarial resistance population

Given the total population of 779,600 in Oyam and Kole districts. Given that, based on Uganda bureau of statistics (UBOS), the total number of pregnant women in the two districts is expected to be 5% of the total population (n = 38,980); the expected rate of parasitemia among pregnant mother is expected to be 27% (n = 10,525) [21]; the expected resistance to sulfadoxine-pirimethamine and artemisinin-derivatives are, respectively, 16% and 20% [16, 18]; using the sample size calculation formula developed by Daniel and colleagues [22] and a margin of error, alpha = 5% the minimum required number of pregnant women diagnosed with malaria is 203. Applying 10% correction factor and assuming an increasing trend the required minimum sample size for this population is 224 cases of microscopically confirmed malaria among pregnant women.

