Delivery	– *Delivery information*: study staff will document details of the delivery, including date and time, type of delivery, estimated blood loss and any maternal, obstetrical or neonatal complications – *Fetal outcomes:* stillbirths, low birth weight, preterm birth – *Infant information:* Apgar score and birth weight with calibrated scales. At the time of delivery, women will undergo repeat rapid HIV testing based on national guidelines. If women are found to have become HIV-infected during pregnancy, both the mother and their newborn will be referred for care following local prevention of mother-to-child transmission guidelines [26] – Analyses of the Placenta Blood by microscopy to detect placental parasitemia

Data will be collected using semi-structured questioners and managed using REDCap electronic data capture tools hosted at “Catholic University of the Sacred Heart”, Rome, Italy [28], and will be recorded on standard study data collection forms and will be reviewed for accuracy and completion. Upon resolution of data forms errors/missing values, the form will be ready for data entry. The obtained results will be entered into a database. A database will be developed to accommodate data entry and management of the study's data. The database will be created with a standard data management software package, such as Microsoft Office. A file for each study form will be created.

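### The cohort is sized on preterm birth by malaria status, but the analysis section names neither preterm birth as an outcome nor malaria as an exposure, so the powered contrast may not be estimated

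*Protocol article*

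**What the plan says.** **Sample size estimation (prospective cohort).** The hypothesis is "Null hypothesis: p1 = p2, (no difference in preterm birth rates"), where p1 refers to women diagnosed with malaria and "p2 is the preterm birth rate among pregnant mothers with no diagnosis of malaria (non-exposed group"). The design values are p1 = 0.075 and p2 = 0.039, with equal groups. The error rates are given as "Assuming a type I error, alpha, of 0.050 for two-sided hypothesis" and "power of the study at 0.80". The result is 705 per group, or 776 per group and 1552 in total after adding 10%.

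**Table 1, Delivery row.** The fetal outcomes to be recorded are "stillbirths, low birth weight, preterm birth".

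**Data analysis.** Behavioural factors and IPTp adherence and regimen are to be related to symptomatic or severe malaria and to "adverse neonatal or foetal outcomes (miscarriage, stillbirth, low birthweight"). Multivariable logistic models are then fitted for those same outcomes. On variable choice: "A forward and backwards stepwise approach will used to include variables into the models", with a limit of P < 0.2. No variable is stated to be kept in regardless. Significance is judged at P < 0.05.

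**The concern.** Neither half of the sized contrast is named where the analysis is described. Preterm birth is absent from the listed foetal outcomes. Malaria, the exposure in the sample-size hypothesis, stands on the outcome side.

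This is not detail left to an analysis plan. The article itself gives a list of outcomes without marking it as examples, and itself fixes the selection method. That list does not match its own sample-size section.

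This is also the only hypothesis with a stated power: the COVID-19 part is a census and the resistance sample is sized on a margin of error. An analyst following the text could report several foetal outcomes and never report the one that justified recruiting 1552 women, or could choose the headline outcome after seeing the data.

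The selection rule adds a smaller problem. If the contrast is fitted under the stated stepwise rule, the data decide whether malaria and each confounder stay in the model.

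**Working it through.** **1. The plan's own figure.** Inputs from Sample size estimation: p1 = 0.075, p2 = 0.039, difference d = 0.036, mean rate 0.057, two-sided alpha 0.05 (z = 1.960), power 0.80 (z = 0.842), ratio 1:1.

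- Uncorrected: n = [1.960 × √(2 × 0.057 × 0.943) + 0.842 × √(0.075 × 0.925 + 0.039 × 0.961)]² / 0.036² = 649.9, so 650.
- Continuity-corrected: n′ = (n/4) × [1 + √(1 + 4/(n·d))]² = (649.9/4) × [1 + √(1 + 4/23.4)]² = 704.3, so **705**. This matches.
- Inflation: 705 × 1.10 = 775.5, so 776; 2 × 776 = **1552**. This matches.

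The arithmetic is sound for preterm birth by malaria status. What is missing is the matching analysis.

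**2. The sections side by side.**

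| Item | Sample size estimation | Table 1, Delivery | Data analysis |
|---|---|---|---|
| Preterm birth | the sizing endpoint | recorded | not listed |
| Stillbirth | – | recorded | listed |
| Low birthweight | – | recorded | listed |
| Miscarriage | – | not listed by name | listed |
| Malaria | exposure | – | outcome only |

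**3. Expected preterm births.**

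- Planned 1:1 split, 705 per group: 705 × (0.075 + 0.039) = 80.4, about **80**.
- If 27% of the cohort is exposed: 1552 × 0.9 = 1397 women; 0.27 × 0.075 + 0.73 × 0.039 = 0.0487; 1397 × 0.0487 = **68**. The 27% is the parasitaemia rate in the resistance-population calculation. Using it as the cohort's exposure rate is an assumption.

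**4. What the P < 0.2 rule does to the malaria term.**

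- If the planned effect is real: with 705 per group the standard error of the difference is about 0.0123, under both the null and the alternative. The chance of passing P < 0.2 is Φ[(0.036 − 1.282 × 0.0123)/0.0123] ≈ 0.95.
- If there is no effect: malaria passes about 20% of the time. About 0.05/0.20 = 25% of the intervals reported after retention would then exclude the true value, so coverage given retention is near 75% rather than 95%.
- An illustrative simulation agrees. Its assumptions are not in the documents: 1410 women, malaria about 1:1, four weak confounders, six noise covariates, backward elimination at P < 0.2, 1000 runs.

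| Quantity | Stepwise | Full fixed model |
|---|---|---|
| False-positive rate for malaria, no effect | 5.9% | 5.1% |
| Retention of malaria, no effect | 20% | always in |
| 95% CI coverage given retention, no effect | 71% | 95% |
| Retention of malaria, odds ratio 2.0 | 95% | always in |

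At odds ratio 2.0 the mean log odds ratio when malaria was retained was 0.75, against a true 0.69. At least one of the six noise covariates was declared significant in 26–29% of runs.

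**The case against.** The strongest reply is that the parenthesis is merely incomplete. The Data analysis section opens with a wider aim covering adverse maternal or foetal outcomes, and Table 1 classes preterm birth as a fetal outcome. Study design says that the prospective cohort is meant to determine malaria-related adverse outcomes. Chi-squared tests are specified for categorical variables and would serve for the two-proportion comparison. This stands in part. A reader might infer that the powered hypothesis will not be tested, but the documents support only that it may not be. The wider phrase does not remove the mismatch, because the outcomes are then spelled out without preterm birth and the models are tied to that list.

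A reader might also infer that stepwise selection invalidates the test of malaria. That is not shown. The rule serves a risk-factor screen, 0.2 is a lenient limit, the false-positive rate for malaria barely moved in the simulation, and a true effect of the planned size would nearly always be retained. The poor coverage applies to runs with no effect in which malaria happened to be kept. What remains is damage to intervals, to confounder control and to claims of independent risk factors.

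Finally, a reader might infer that miscarriage is analysed but never collected. It is not named in the Delivery row, but outcomes are also assessed at discharge after pregnancy-related admissions, complications are recorded at delivery, and the ethics section anticipates pregnancy losses. It can plausibly be captured.

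**Conclusion.** The concern holds as an inconsistency within the article. The cohort is sized solely on preterm birth by malaria status, and preterm birth is collected, yet the analysis section names neither that outcome nor malaria as an exposure. The powered contrast may therefore not be estimated; the documents do not establish that it will be omitted.

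The sample size needs no change on this account. About 80 preterm births are expected on the cohort's own assumptions, or about 68 if 27% exposure is assumed. Letting P < 0.2 decide the model for this contrast is a secondary weakness. Its effect on malaria's own test is small (5.9% against 5.1% false positives, under simulation assumptions from outside the documents), and its main cost is in intervals and confounding.

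**What to change.** 1. Add preterm birth to the outcomes in Data analysis, and name malaria in pregnancy versus none, on preterm birth, as the primary comparison, reported with a 95% CI.
2. For that comparison, fit a fixed model: malaria always in, with a prespecified set of baseline confounders that are already collected. Examples are age, gravidity, HIV status, nutritional status, net use at recruitment and study site.
3. Do not adjust that model for the total number of IPTp doses received. Early delivery cuts the count short, so the outcome partly determines the covariate. The count is also tied to HIV status, since the Background describes sulfadoxine-pyrimethamine IPTp for HIV-negative women and co-trimoxazole prophylaxis for HIV-positive women.
4. Stepwise screening of other risk factors may stay, labelled exploratory.

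The cost is a change of wording, with no new data and no change in sample size. Giving up data-driven pruning makes the intervals slightly wider.

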### Pregnancy associated malaria

#### Intermittent preventive treatment

In hyperendemic areas, pregnancy is a risk factor for both acquisition [4] of *P. falciparum* infection and for development of severe malaria [5]. Younger women, primi- or secundigravidae and HIV + women are particularly at risk [6]. Adverse outcomes for mothers and their infants include maternal anemia, low birthweight, prematurity, placental malaria, infant malaria, infant anemia and congenital malaria. Furthermore, adverse events are exacerbated by poor maternal nutritional status [7] and HIV coinfection [8].

Apart from consistent use of ITN, malaria control in this population is based on two pillars: intermittent preventive treatment of asymptomatic women and appropriate management in case of illness [9]. IPTp with sulfadoxine-pyrimethamine (SP) is still highly cost-effective in preventing the adverse consequences of malaria on maternal and foetal outcomes, even in areas with a high prevalence of quintuple mutant parasites [10], but coverage remains unacceptably low in several African countries [11]. For HIV-negative pregnant women, IPTp consists in the administration of at least three doses of SP (1500 mg sulfadoxine/75 mg pyrimethamine), in three antenatal care visits, starting early in the second trimester and at least four weeks apart [9].

In HIV negative women, a promising alternative to SP for IPTp is dihydroartemisinin-piperaquine (DHA-PPQ, 3 full strength tabs, 40 mg/320 mg, given once a day for 3 consecutive days), that showed to be more efficacious in reducing maternal malaria parasitemia and anemia at delivery, stillbirths and early infant mortality. In fact, SP efficacy may be decreased in areas with very high drug resistance and consistent presence of sextuple mutant haplotypes of *P. falciparum* [12]. However, there is no consensus as to the level of resistance at which SP-IPTp should be discontinued and an alternative regimen substituted.

For HIV positive patients, the current WHO guidelines recommend daily co-trimossazole prophylaxis.

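### The stepwise risk-factor models for birth outcomes keep no variable out for lying on the causal path, so malaria may enter beside IPTp and net use and shift their coefficients towards the null

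*Protocol article*

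**What the plan says.** The Data analysis section of the protocol article gives the aim: "Association analysis will be carried out to identify risk factors for Plasmodium infection and adverse maternal or foetal outcomes". It then names the exposures: "We will compare behavioural factors and adherence to IPTp (and type of IPTp regimen) to the incidence of symptomatic/severe malaria and adverse neonatal or foetal". The birth outcomes listed there are miscarriage, stillbirth and low birthweight. The adjusted analysis follows: "Multivariable logistic regression models will be used to identify independent risk factors for the same clinical outcomes". The entry rule is also stated: "A forward and backwards stepwise approach will used to include variables into the models, with a limit of P < 0.2". The section describes no model built around a particular exposure and no variable withheld because it is a consequence of one.

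Two other places show how malaria relates to these exposures and outcomes. The Background section on intermittent preventive treatment says that SP-based IPTp is "still highly cost-effective in preventing the adverse consequences of malaria on maternal and foetal outcomes". It presents nets as a further malaria control measure and lists the harms of infection: "Adverse outcomes for mothers and their infants include maternal anemia, low birthweight, prematurity, placental malaria, infant malaria, infant anemia and congenital malaria". The Sample size estimation section defines the exposed group as women diagnosed with malaria and compares their preterm birth rate with that of undiagnosed women.

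Table 1 shows when the downstream variables arise: malaria is tested at every antenatal visit, haemoglobin at first contact and at 26 weeks, and placental parasitaemia at delivery.

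**The concern.** A selection rule based on P-values cannot tell a confounder from a mediator. A variable on the path from IPTp to birth outcome predicts the outcome well, so the rule favours it. Once malaria is in the model, the IPTp coefficient compares women with the same malaria status. It then measures only what IPTp does by other routes, and the same holds for net use. Adjusting for malaria can also bring in bias from unmeasured causes shared by malaria and the birth outcome.

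At stake is what the adjusted estimate for the main preventive measures means. A reader would take an independent effect of IPTp on low birthweight or stillbirth as the effect of IPTp, when it may be only the part that does not pass through malaria.

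**Working it through.** **The plan's own figure.** Inputs from Sample size estimation: p1 = 0.075, p2 = 0.039, two-sided alpha 0.05, power 0.80, equal groups.
- n = [1.96 × √(2 × 0.057 × 0.943) + 0.8416 × √(0.075 × 0.925 + 0.039 × 0.961)]² / 0.036² = 650 per group.
- With continuity correction: 650/4 × [1 + √(1 + 4/(650 × 0.036))]² = 705, as stated.
- 705 × 1.10 = 775.5, so 776 per group and 1552 in total, as stated. These rates are used below.

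**Would malaria pass P < 0.2 if offered?** Preterm birth stands in for the birth outcomes, because the document gives no malaria-specific rates for the others. The probability is Φ[(0.036 − 1.2816 × SE0)/SE1], where SE0 uses the pooled risk and SE1 the separate risks.
- 705 against 705: SE0 = 0.01235, SE1 = 0.01231, giving 0.95.
- 27% of 1410 women with malaria (the document's parasitaemia figure; 381 against 1029): SE0 = 0.01291, SE1 = 0.01479, giving 0.91.
- In simulated logistic models with IPTp also included, malaria passed in 0.88 to 0.93 of runs.

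**What happens to the IPTp coefficient?** Assumptions, not in the document: 40% of women have full IPTp (the Background says only that coverage of three or more doses is below 48%), and IPTp halves malaria risk. From the document: 27% malaria overall, outcome risk 7.5% with malaria and 3.9% without.
- Malaria risk without IPTp: 0.27/(0.6 + 0.4 × 0.5) = 0.3375. With IPTp: 0.16875.
- Outcome risk without IPTp: 0.039 + 0.036 × 0.3375 = 0.0512. With IPTp, if there is no other path: 0.039 + 0.036 × 0.16875 = 0.0451.
- Total odds ratio: (0.0451/0.9549)/(0.0512/0.9488) = about 0.88. With malaria in the model it is 1.00, by construction.
- With an added direct odds ratio of 0.85, the risks under IPTp become 0.0645 with malaria and 0.0333 without, so the outcome risk is 0.0386. The total odds ratio is about 0.74, and 0.85 with malaria in the model.

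**Sensitivity.** These are simulated logistic models at 48% coverage and 1410 women with no direct effect. The malaria risks by IPTp status are assumptions.
- Malaria 35% without IPTp and 18% with it: mean odds ratio 0.87 alone, 0.99 with malaria in the model.
- Malaria 70% without and 30% with it: 0.76 alone, 1.00 with malaria in the model.

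**Precision.** In the no-other-path scenario with 1410 women (564 with IPTp, 846 without), the risk difference is 0.0061 and its standard error 0.0117, a ratio of 0.52. Two-sided power at 0.05 is Φ(0.52 − 1.96) + Φ(−0.52 − 1.96) = about 8%.

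**The case against.** The strongest reply is that the entry of malaria is inferred. The section lists no candidate covariates, and it names symptomatic and severe malaria as outcomes. A condensed article may leave candidate lists to a fuller document. This stands as a limit: entry is permitted and probable, not established. It does not remove the point, because the aim, the model type and the selection rule are stated, and that rule has no safeguard for variables on the path. Malaria is the exposure in the study's own sample size calculation, so it is a natural candidate.

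Second, comparisons of IPTp with the outcomes are also planned outside the regression, and these would show an effect that runs through malaria. That is a partial answer only, since they are not adjusted for confounders.

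Third, a malaria-adjusted coefficient is a legitimate quantity. It is, if labelled as a direct effect; the plan does not label it so.

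Fourth, with power of about 8%, a null IPTp result is likely whichever model is used. This is correct, and it limits the claim to bias in the estimate.

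A reader might go further and infer that the whole IPTp effect will vanish and that the study will then report SP failure. The documents support neither inference. Complete loss follows only from assuming no path other than malaria. Resistance to SP is assessed by genotyping in a separate subpopulation, not from an IPTp coefficient.

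**Conclusion.** The concern holds in a limited form. As written, the selection rule allows malaria and other consequences of the exposure into the birth-outcome models, and at the planned rates malaria would usually pass if offered. The IPTp and net-use coefficients would then be direct effects, shifted towards the null. In the illustrations the shift is from about 0.88 to 1.00, or from about 0.74 to 0.85. These sizes rest on the assumed coverage, the assumed halving of malaria, and preterm rates standing in for other outcomes. If the exposures protect by preventing malaria, the direction of the shift does not depend on those figures.

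The point does not touch the estimate for malaria itself from adjusting for IPTp or nets, which lie upstream of it. Later haemoglobin in a model with malaria as the outcome is a different error: there it is a consequence of the outcome, not a mediator.

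**What to change.** Reword the regression paragraph so that a separate model is fitted for each main exposure, with covariates chosen as confounders that precede that exposure.

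- **IPTp and net use as exposures:** do not offer malaria, parasitaemia, placental parasitaemia, haemoglobin or gestational age at birth when they arise after the exposure began. The timing condition matters. Women enrol at any gestational age and are tested at recruitment, so malaria or haemoglobin measured there before the first IPTp dose is a possible confounder and may stay available.
- **Malaria as exposure:** do not offer haemoglobin taken after the infection or other birth outcomes.
- **Reporting:** give any malaria-adjusted IPTp estimate only as a secondary direct effect, labelled as such.

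The cost is one reworded paragraph and a few extra models. No new data are needed and the sample size does not change.

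### Stepwise selection at P < 0.2 with no forced covariates can drop HIV, age or gravidity, which the protocol itself names as risk factors, and the HIV-negative set for the IPTp comparisons is not stated

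*Protocol article*

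**What the plan says.** The Data analysis section of the protocol article sets out an association analysis: "We will compare behavioural factors and adherence to IPTp (and type of IPTp regimen) to the incidence of symptomatic/severe malaria" and to adverse neonatal or foetal outcomes (miscarriage, stillbirth, low birthweight). It continues: "Multivariable logistic regression models will be used to identify independent risk factors for the same clinical outcomes". The covariates are chosen by a rule: "A forward and backwards stepwise approach will used to include variables into the models", "with a limit of P < 0.2". No variable is named as always included, and no restriction or stratification by HIV is given.

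The background section on intermittent preventive treatment supplies the subject knowledge. It singles out "Younger women, primi- or secundigravidae and HIV"-positive women as at higher risk, and says that HIV coinfection worsens adverse events. It also ties chemoprevention to HIV status: "For HIV-negative pregnant women, IPTp consists in the administration of at least three doses of SP", with DHA-PPQ discussed as an alternative in the same group, whereas "For HIV positive patients, the current WHO guidelines recommend daily co-trimossazole prophylaxis".

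Under Eligibility criteria, the cohort takes all pregnant women and excludes only those in labor or delivery, so HIV-positive women are enrolled. Table 1 shows that age, number of previous pregnancies, gestational age and HIV status are all recorded at recruitment.

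**The concern.** A P-value rule asks whether a covariate is detectably related to the outcome in this sample. That is a different question from whether leaving it out biases the exposure effect. With few events, an uncommon but real confounder often fails the test and is left out, while some irrelevant variables pass by chance. Confidence intervals from the selected model are then computed as if it had been chosen in advance.

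HIV is the exposed case. It is uncommon (an assumption; the documents give no prevalence), and the protocol links it to chemoprevention and to outcome. If it is dropped, part of its effect can be credited to IPTp. When birth outcomes are modelled on malaria, dropping age, gravidity or HIV carries the same risk for the malaria estimate, which is the contrast that sized the cohort.

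**Working it through.** **1. The plan's own figure.** Inputs from Sample size estimation: p1 = 0.075, p2 = 0.039, two-sided alpha 0.05, power 0.80, equal groups. The two-proportion formula gives 649.9 per group without and 704.3 with continuity correction, hence the stated 705. Then 705 × 1.10 = 775.5, rounded up to 776, and 2 × 776 = 1,552. The figure reproduces. Evaluable women: 2 × 705 = 1,410.

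**2. Events.** 705 × 0.075 + 705 × 0.039 = 52.9 + 27.5 = about 80 preterm births. The documents give no rates for the outcomes named in Data analysis, so 80 is a yardstick. I also use 60, and 141 (a 10% outcome); both are assumptions.

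**3. Chance that a real confounder misses P < 0.2.** One binary covariate with prevalence π and odds ratio OR, single-covariate Wald approximation:

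- n1 = 1,410π, n0 = 1,410(1 − π); p0 and p1 are the outcome risks without and with the factor, set to give the stated number of events
- SE² = 1/[n1·p1(1 − p1)] + 1/[n0·p0(1 − p0)]
- m = ln(OR)/SE
- P(missed) = Φ(1.2816 − m) − Φ(−1.2816 − m)

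Example: π = 0.07, OR = 1.7, 80 events. n1 = 98.7, n0 = 1,311.3, p0 = 0.0543, p1 = 0.0890, SE = 0.374, m = 0.5306/0.374 = 1.419, P(missed) = 0.44.

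| Events | π = 7%, OR 1.7 | π = 7%, OR 2.0 | π = 35%, OR 1.7 | π = 35%, OR 2.0 |
|---|---|---|---|---|
| 60 | 51% | 33% | 23% | 9% |
| 80 | 44% | 25% | 16% | 4% |
| 141 | 30% | 12% | 5% | 0.5% |

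Simulated backward elimination at P < 0.2 with 60 to 80 events and eight noise variables agrees for the 7% factor: dropped in 46–48% of runs at OR 1.7 and 24–33% at OR 2.0.

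**4. Noise retained.** With eight independent irrelevant candidates (assumed), the chance that at least one passes is 1 − 0.8⁸ = 0.83. The simulation gave 82–86%.

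**5. Conditional on pooling by HIV status.** Suppose HIV-positive and HIV-negative women were analysed together and the regimen had no true effect. Assumptions: 1,410 women, 10% outcome, HIV prevalence 5–8%, HIV odds ratio 1.5–2.0, and 80–95% of HIV-positive and 2% of HIV-negative women on the non-SP regimen. Stepwise selection left HIV out in 28–65% of runs, and the false-positive rate for regimen was 0.09–0.20. With HIV forced in it was 0.04–0.05. If HIV status fully determined SP versus co-trimoxazole, even a forced term could not separate them.

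**6. Room for a fixed model.** Exposure, age, gravidity, HIV and gestational age as one term each, plus two terms for three sites, make 7 parameters: 80/7 = 11.4 events per parameter, or 60/7 = 8.6.

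**The case against.** The strongest reply has four parts.

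- **The purpose is to find risk factors.** The stated aim is to identify independent risk factors, P < 0.2 is a lenient limit, and symptomatic malaria is itself an outcome in some models. This stands in part: malaria can be a fixed term only where birth outcomes are modelled. But the same section sets IPTp against outcomes, and calling a factor independent still requires the known confounders to be in the model.
- **The text does not say that IPTp is compared across all women.** This stands. A reader might infer that the regimen comparison is simply a comparison by HIV status. The background uses the term IPTp only for SP and DHA-PPQ in HIV-negative women, so regimen type can mean a contrast within that group.
- **Adherence is not defined as a count of SP doses.** This also stands. A reader might infer that HIV-positive women would be classed as non-adherent, but Table 1 records adherence to chemoprevention more broadly and no coding is given. No bias figure should be built on that coding.
- **Common, strong confounders usually survive.** This is true: at 80 events a 35%-prevalence factor with OR 2.0 is missed only 4% of the time. For age and gravidity the protocol documents a link to malaria risk, but none to IPTp regimen or adherence.

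A separate analysis plan may add detail, but the stepwise rule is stated here and is not an omission.

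**Conclusion.** The point holds in this form: the protocol fixes a selection rule that can discard confounders it has itself named. For an uncommon factor such as HIV, the risk is roughly a quarter to a half with 60 to 80 events, falling to 12–30% with 141. It is small for common, strong factors. These figures rest on an assumed 7% prevalence and odds ratios of 1.7 to 2.0, and on preterm birth as a guide to event numbers.

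It would go too far to say that the IPTp and malaria effects are confounded. The documents show only that they can be left so. The false-positive rates of 0.09–0.20 apply only if women are pooled across HIV status, which the text neither states nor excludes. The matter should be put right before analysis; it does not undermine the design or the sample size.

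**What to change.** Replace the stepwise sentence with a pre-specified model for each outcome: the exposure of interest (IPTp adherence or regimen; malaria when birth outcomes are modelled) plus age, gravidity, HIV status, site and gestational age at enrolment. Label any stepwise model exploratory. For outcomes with too few events for seven parameters, state a penalised fit or a shorter fixed list in advance.

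State that the IPTp regimen and adherence comparisons are run in HIV-negative women, by the recruitment test, and that HIV-positive women are described separately. HIV then leaves the covariate list for those models. Say how adherence is defined.

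The cost is analysis wording: the covariates are already collected and the sample size of 1,552 is unchanged. The small downside is that HIV-positive women leave the IPTp contrast and a few degrees of freedom are committed in advance.
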